### Statistical analysis

For the purpose of the study, we computed a sample size of 56 patients, given an α error of 5% (one-sided) and a β error of 80%, with a standard deviation for the primary outcome equal to 15 mmHg and a noninferiority limit of 10 mmHg [35]. After considering potential drop-outs (30%) [35] and an increase in sample size for nonparametric analysis (15%), the final computed sample size was 80 patients (40 per group).

An independent investigator, blinded to treatment allocation, will undertake all statistical analyses on an intention-to-treat basis. After checking the Gaussian distribution, continuous data will be presented as mean (standard deviation) or median (25th–75th IQR).

Categorical data will be expressed as count and percentage. Continuous data will be compared by the Mann–Whitney *U* test or the Student *t* test, and categorical data by the chi-square test or the Fisher exact test [46]. The Kruskal–Wallis test will be used to check between-group differences at baseline, 2 h and 6 h. Friedman’s test or repeated-measures ANOVA will be used to check within-group differences at different time points. *p* < 0.05 will be considered significant.

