**Methods:**

We will enroll adult patients with acute hypercapnic respiratory failure, as defined by arterial pH between 7.25 and 7.35 and PaCO_2_ ≥ 55 mmHg. Patients will be randomly assigned 1:1 to receive NIV or HFNT. NIV will be applied through a mask with a dedicated ventilator in pressure support mode. Positive end-expiratory pressure will be set at 3–5 cmH_2_O with inspiratory support to obtain a tidal volume between 6 and 8 ml/kg of ideal body weight. HFNT will be initially set at a temperature of 37 °C and a flow of 60 L/min. At 2 and 6 h we will assess arterial blood gases, vital parameters, respiratory rate, treatment intolerance and failure, need for endotracheal intubation, time spent under mechanical ventilation (both invasive and NIV), intensive care unit and hospital length of stay, and hospital mortality.

Based on an α error of 5% and a β error of 80%, with a standard deviation for PaCO_2_ equal to 15 mmHg and a noninferiority limit of 10 mmHg, we computed a sample size of 56 patients. Considering potential drop-outs and nonparametric analysis, the final computed sample size was 80 patients (40 per group).

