## Methods

### Study design

This is an investigator-initiated, unblinded, multicenter, noninferiority, randomized controlled trial. Randomization has been achieved using a computer-generated randomization sequence, generated by an independent investigator not otherwise involved in the trial, with an allocation ratio of 1:1 and with a permuted block method. A single randomization list was created for all participants. Allocation concealment has been maintained by using sequentially numbered sealed opaque envelopes. Each envelope contains the allocation of the patient to either control (NIV) or intervention (HFNT), with a unique patient identifier code. The randomization is based on a centralized phone call system. Due to the research design, neither the individual collecting data nor the patient can be blinded to treatment allocation.

The study was prospectively registered with ClinicalTrials.gov in December 2017 (identifier: NCT03370666). This protocol has been designed in accordance with the Standardized Protocol Items: Recommendations for Interventional Trials (SPIRIT) guidelines and checklist (Additional file 1). A schedule for enrolment, intervention and assessment (SPIRIT figure) is outlined in Fig. 1. A CONsolidated Standards of Reporting Trials (CONSORT) diagram is shown in Fig. 2.

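### The 80 patients cover the 30% drop-out allowance alone; the stated 15% nonparametric increase is not in the total, and power is misprinted as a β error of 80%

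*Protocol article*

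**What the plan says.** The Statistical analysis section of the protocol article states the error rates in these words: "given an α error of 5% (one-sided) and a β error of 80" percent. The remaining inputs are "a standard deviation for the primary outcome equal to 15 mmHg and a noninferiority limit of 10 mmHg". On that basis the article reports: "we computed a sample size of 56 patients". The enlargement is described next: "After considering potential drop-outs (30%) [35] and an increase in sample size for nonparametric analysis (15%), the final computed sample size was 80 patients". That makes two arms of 40. The Study design section sets the allocation at 1:1.

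The Methods part of the abstract repeats the mislabelled power ("Based on an α error of 5% and a β error of 80" percent) and the total, again crediting it to both allowances: "Considering potential drop-outs and nonparametric analysis, the final computed sample size was 80 patients (40 per group"). The abstract gives no percentages for the two allowances, so only the Statistical analysis section can be checked numerically.

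**The concern.** The article prints the base, both allowances and the result, so the reader can redo the sum, and it does not come out. The total equals the base enlarged for drop-out alone, yet the text says that it also contains a reserve for nonparametric analysis. That analysis is a live possibility: the same section names the Mann–Whitney test as one of two tests for continuous data, and the primary endpoint, PaCO2 at 2 h, is continuous.

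In a noninferiority trial, low power means that a treatment which truly is noninferior may fail to be shown so. Readers would take it that 80% power survives both a 30% loss and a rank-based analysis, when the enrolment supports only one of these.

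Separately, the β error is the probability of missing a true effect. A value of 80% describes a trial with 20% power, so a core design parameter is stated wrongly in two places.

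**Working it through.** **Inputs** (Statistical analysis section unless noted): one-sided α 5%; SD 15 mmHg; margin 10 mmHg; 1:1 allocation (Study design); base 56; drop-out 30%; nonparametric increase 15%; final total 80. The true difference is not stated and is taken as 0, the value that reproduces 56.

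**1. The base of 56.**

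n per arm = 2 × (z₀.₉₅ + z₀.₈₀)² × SD² / margin² = 2 × (1.645 + 0.842)² × 15² / 10² = 27.8, rounded up to 28. The total is 56, which reproduces the plan's figure at 80% power.

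**2. The β error read literally.** With 20% power, z₀.₂₀ = −0.842 replaces z₀.₈₀. The same formula gives 2.9, or 3 per arm. So 56 was computed with β = 20%, and the printed 80% is the power.

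**3. From 56 to the final total.**

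| Route | Result |
|---|---|
| Drop-out only: 56 / 0.70 | 80.0 |
| Percentages added: 56 × 1.45 | 81.2 |
| Both as multipliers: 56 × 1.30 × 1.15 | 83.7 |
| 15% as multiplier, drop-out as divisor: 56 × 1.15 / 0.70 | 92.0 |
| Both as divisors: 56 / 0.70 / 0.85 | 94.1 |

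Only the drop-out-only route gives 80.

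**4. A check that does not depend on the route.** If 30% of 80 are lost, 80 × 0.70 = 56 remain. That is the base before any nonparametric increase.

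**5. Power under both of the plan's own allowances.** The 28 evaluable per arm are worth 28 / 1.15 = 24.35 per arm.

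Power = Φ(√(24.35 / 2) × 10 / 15 − 1.645) = Φ(2.326 − 1.645) = Φ(0.681) = 0.752. The t-based calculation gives 0.741.

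**6. Drop-out covered if the 15% is honoured.** The evaluable number needed is 56 × 1.15 = 64.4, and 1 − 64.4 / 80 = 0.195, that is 19.5%.

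**The case against.** **The shortfall needs several things to happen together.** About 75% power requires the full 30% loss, the rank test and the full 15% penalty. Other cases are kinder (normal approximation):

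| Analysis | Lost | Power |
|---|---|---|
| t test | none | 90.9% |
| t test | 30% | 80.2% |
| 15% penalty | none | 87.2% |
| 15% penalty | 10% | 84.0% |
| 15% penalty | 15% | 82.1% |
| 15% penalty | 30% | 75.2% |

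If the data are in fact normal, the rank test has a relative efficiency of about 0.955, and power at 30% loss is about 78.6%. Moreover, the endpoint is a blood gas at 2 h analysed by intention to treat, so patients who stop or switch treatment need not be missing. All this is correct, and it means the power claim must be conditional. It does not rescue the sentence: each kinder case sets aside or softens one of the two allowances that the plan says it has made.

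**Adding the percentages comes close.** 56 × 1.45 = 81.2 is within 1.2 patients of 80, so the figure may have been reached that way and rounded down. On that reading the shortfall is 2 patients (82 against 80), not 12. But multiplying by 1.30 does not cover a 30% loss: 56 × 1.30 = 72.8, of which 72.8 × 0.70 = 51 remain. Step 4 of the working holds however 80 was obtained. What stands is that 92 is the total under the usual convention and is not a figure the document fixes.

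**The β wording is a slip.** Agreed. It had no effect on the calculation, and it needs only an editorial correction.

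**Conclusion.** The point holds. The base of 56 is right; the final 80 contains the drop-out allowance and nothing for the nonparametric analysis, contrary to what the Statistical analysis section and the abstract say. Under the plan's own two allowances, power is about 75% (0.752 normal, 0.741 t-based) against the intended 80%, a loss of about 5 percentage points. Equivalently, the drop-out that can be absorbed is 19.5% instead of 30%.

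These figures rest on a true difference of zero, SD 15 mmHg, and the 15% acting as a divisor of the effective sample size. The loss is moderate, and it disappears if the t test is used or if fewer than about a fifth of patients are lost. The β error of 80% is a mislabel of 80% power with no numerical consequence, but it should not stand in either place.

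**What to change.** Correct the Statistical analysis section and the abstract together:

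- Replace the β error of 80% with 80% power (β = 20%).
- Say what 80 patients cover. Either 30% drop-out only, with about 75% power if the nonparametric analysis carries the 15% penalty; or the 15% increase with 19.5% drop-out.
- If both allowances are to be kept as stated, give the total that carries them and the convention used. With the 15% as a multiplier and drop-out as a divisor this is 92 (46 per group), 12 more than now planned.

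The first two changes cost only a text correction and a somewhat less favourable stated power. They need no additional patients and no change to the analysis.

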### Intervention group

Patients randomized to the intervention group will receive HFNT (Optiflow and MR850 or AIrVO_2_™; Fisher & Paykel Healthcare, Auckland, New Zealand), initially set at 60 L/min and a temperature of 37 °C. In the case of discomfort, the flow and/or temperature will be downregulated to the most tolerated setting. In the HFNT group, a rescue NIV treatment will be allowed in the case of worsening of respiratory failure and/or treatment failure, before proceeding with an eventual endotracheal intubation and invasive mechanical ventilation.

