### Control group

Patients randomized to the control group will receive NIV applied through a total full-face or oro-nasal mask. The ventilator will be set in pressure support ventilation (PSV) mode, with positive end-expiratory pressure (PEEP) between 3 and 5 cmH_2_O. The inspiratory pressure support will be regulated in order to achieve a measured or estimated tidal volume equal to 6–8 ml/kg of ideal body weight [35]. The treating physicians, based on local availability, will choose the ventilators used to deliver NIV.

In both groups, treatment other than ventilatory support will be supplied according to current guidelines [1]. Sedatives will be allowed to improve the patient’s comfort and tolerance of the interfaces. The inspired oxygen fraction (FiO_2_) will be set to maintain a peripheral saturation (SpO_2_) target between 88 and 92% [1]. In the case of treatment interruption due to any reason, patients will receive oxygen supply through a Venturi mask to achieve the same SpO_2_ target. During study interventions, patients will be monitored by at least continuous SpO_2_, electrocardiogram and noninvasive blood pressure.

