### Study endpoints

The primary endpoint of the study will be to evaluate whether HFNT is noninferior to NIV in reducing PaCO_2_, at 2 h after the group allocation, in patients with exacerbation of COPD and mild-to-moderate respiratory acidosis. The secondary endpoints will be: noninferiority of HFNT to NIV in reducing PaCO_2_ at 6 h after randomization; dyspnea score; treatment failure rate; discomfort related to the interface or to symptoms related to airway and mouth dryness; respiratory rate; need for endotracheal intubation; time spent under mechanical ventilation (both invasive and NIV); ICU and hospital length of stay; and hospital mortality.

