### Data collection and outcome assessment

For each patient, we will collect anthropometric data (age, gender, weight and height) and baseline characteristics (the Simplified Acute Physiology Score (SAPS II), the Kelly-Matthay score [36], the Charlson index [37] and the Richmond Agitation Sedation Scale (RASS) score [38]). Furthermore, soon before randomization we will record vital parameters (heart rate, blood pressure, breath frequency and temperature), the amount of secretions, the presence of dyspnea (as reported by the patient through the Borg scale) [39] and arterial blood gases (ABGs) at patient inclusion.

At 2 and 6 h after the patient’s randomization to receive NIV or HFNT, we will collect all vital parameters, ABGs, the RASS score, the Kelly-Matthay score [36], the grade of dyspnea and the need for sedatives. Sedation will be allowed to increase tolerance to the treatment [40, 41]. Moreover, we will record: the settings of NIV and HFNT; the discomfort related to the interface, as assessed through a 11-point Numeric Rating Scale (NRS) [15, 42, 43]; and the intolerance to the interface due to flow, temperature, noise, claustrophobia, sweating, tightness, airway dryness, vomiting gastric distension, ocular irritation or skin breakdown, separately [42, 44, 45].

We will also record: the rate of treatment intolerance, as defined by the inability of the patient in continuing NIV or HFNT treatment; the rate of treatment failure, as defined by the presence of PaCO_2_ worsening or reduction < 10 mmHg from baseline assessment, or worsening or no improvement of dyspnea, or respiratory rate > 30 breaths/min; need for endotracheal intubation; time spent under mechanical ventilation (both invasive and NIV); ICU and hospital length of stay; and hospital mortality.

The decision to intubate the patient will be taken by the physician in charge of the patient, in the case of the presence of one of the following criteria: respiratory arrest, respiratory apnea or pauses with loss of consciousness, severe agitation, bradycardia (< 50 beats/min) with loss of consciousness, hemodynamic instability with systolic arterial pressure < 70 mmHg, need for invasive mechanical ventilation due to worsening in arterial blood gases and pH, need for suctioning due to unmanageable secretions or intolerance to all of the interfaces (including shift of treatment to NIV in the HFNT group).

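### Every analysis is fixed as intention-to-treat although HFNT patients may be rescued with the control treatment, which favours a noninferiority claim if HFNT is worse, mainly at 6 h and less at 2 h

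*Protocol article*

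**What the plan says.** The Study design section describes the trial: "This is an investigator-initiated, unblinded, multicenter, noninferiority, randomized controlled trial". The Study endpoints section sets the primary comparison of PaCO2 "at 2 h after the group allocation" and lists as a secondary endpoint "noninferiority of HFNT to NIV in reducing PaCO_2_ at 6 h after randomization". The Statistical analysis section states that the independent investigator "will undertake all statistical analyses on an intention-to-treat basis". The article names no other analysis set and no rule for a PaCO2 measured after rescue.

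Under Intervention group: "In the HFNT group, a rescue NIV treatment will be allowed in the case of worsening of respiratory failure and/or treatment failure". No time limit is attached, so rescue may come before either sample. Under Control group: "Patients randomized to the control group will receive NIV applied through a total full-face or oro-nasal mask". The rescue is therefore the comparator. No switch from NIV to HFNT is described; interrupted treatment in either arm is covered by Venturi-mask oxygen.

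The Data collection and outcome assessment section records "the rate of treatment failure, as defined by the presence of PaCO_2_ worsening or reduction < 10 mmHg from baseline assessment". Worsening or unimproved dyspnea, or a respiratory rate above 30 breaths/min, also counts as failure. After baseline, the scheduled blood gases are at 2 h and 6 h.

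**The concern.** In a superiority trial, crossover to the comparator usually dilutes a real difference, so ITT is the cautious choice. In a noninferiority trial the same dilution works for the claim. Here switching runs in one direction only, onto the control treatment, and one failure criterion is a poor response on the outcome variable itself. The HFNT patients doing worst on PaCO2 are thus those most likely to have it measured on NIV. If HFNT is truly worse, more rescue makes it look closer to NIV.

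The two samples are not equally exposed. By 6 h, the 2 h gas has been available to show a fall of less than 10 mmHg. Before 2 h no scheduled gas after baseline exists, so early rescue would rest mainly on dyspnea, respiratory rate or evident worsening. Unscheduled gases are not excluded.

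At stake is the meaning of a positive result. The Discussion would use it to support HFNT as an alternative to NIV. A PaCO2 obtained on NIV does not support that.

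**Working it through.** **Inputs from the Statistical analysis section:** margin 10 mmHg, SD 15 mmHg, one-sided alpha 5%, 56 patients before inflation and 80 (40 per group) after it. Power is taken as 80%, the evident meaning of the stated β error of 80%.

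**The plan's own figure.** n per arm = 2 × [15 × (1.645 + 0.842) / 10]² = 27.8, rounded up to 28, or 56 in total. This matches, so the sample-size calculation is not at issue.

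**Assumptions not in the documents:**
- D: true PaCO2 disadvantage of HFNT without rescue. D = 10 mmHg puts it exactly at the margin, where the false-claim rate should be 5%.
- c: share of HFNT patients on rescue NIV before the sample.
- r: share of the deficit that rescue removes by the time of the sample (1 = full, 0.5 = half).
- The SD stays at 15 mmHg, and the normal approximation holds.

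**Formulas.**
- Difference seen under ITT = D × (1 − r × c)
- SE = 15 × √(2/n): 3.354 for n = 40 per arm, 4.009 for n = 28
- P(claim noninferiority) = Φ{[10 − D(1 − r × c)] / SE − 1.645}

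**Worked case.** D = 10, c = 20%, r = 1, n = 40: the ITT difference is 10 × 0.8 = 8 mmHg, and (10 − 8)/3.354 − 1.645 = −1.049. Φ(−1.049) = 0.147, against 0.050 without rescue.

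**False noninferiority rate with D = 10 mmHg:**

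| Share rescued before the sample | 40 per arm, full recovery | 28 per arm, full recovery | 40 per arm, half recovery |
|---|---|---|---|
| 0% | 5.0% | 5.0% | 5.0% |
| 10% | 8.9% | 8.1% | 6.7% |
| 20% | 14.7% | 12.6% | 8.9% |
| 30% | 22.6% | 18.5% | 11.6% |

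The 28-per-arm column is the plan's number before inflation, relevant because 30% drop-out is allowed for.

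**A larger true deficit.** With D = 12 mmHg, 40 per arm and full recovery, the rates are 1.3%, 3.0%, 6.4% and 12.1% at 0, 10, 20 and 30% rescued. They start lower but rise in the same way. With D = 0 the formula gives no shift: the bias needs HFNT to be truly worse.

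**The case against.** **ITT answers a legitimate question.** The Background speaks of first-line treatment, and starting with HFNT and rescuing with NIV is a real policy. This stands, and ITT should stay. But the stated aim is whether HFNT is noninferior in reducing PaCO2, which is a claim about HFNT itself.

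**Rescue would be partly visible.** Treatment failure, intubation and time under mechanical ventilation, including NIV, are secondary endpoints, so heavy NIV use in the HFNT arm should show. This too stands, but it does not correct the PaCO2 test.

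**Supportive analyses are often left to a SAP, which is not shown.** Leaving out a per-protocol set would be no finding. The article goes further and fixes all analyses as ITT. That is a stated choice.

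**A reader might infer that half the HFNT arm will be on NIV.** If the mean PaCO2 fall were 10 mmHg, about half would meet the PaCO2 criterion, and at 50% rescued the formula gives 43.9% (40 per arm, full recovery). The documents do not support this. They give no expected fall, and rescue is allowed, not required. Nor could that figure describe the 2 h primary test, whose own sample is the first scheduled gas on which the criterion can be read.

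**A reader might also infer that a per-protocol analysis settles the matter.** Excluding rescued patients removes the HFNT failures and can itself favour HFNT.

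**Conclusion.** The concern holds in a limited form. A stated rule, ITT for everything, meets one-way rescue with the comparator, and if HFNT is truly worse the bias runs towards the trial's claim. No safeguard is stated, and the limitations in the Discussion do not mention it.

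The exposure is greatest for the 6 h secondary test. For the 2 h primary test it is smaller and unknown, but not zero, because rescue before 2 h is permitted. The documents do not support calling the primary result invalid.

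The size is conditional. For 10 to 30% rescued and a true deficit equal to the margin, the false-claim rate is about 7 to 12% with half recovery and about 8 to 23% with full recovery, against 5% nominal. The direction follows from the plan; the rescue rate and the degree of recovery are assumptions.

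**What to change.** Replace the statement that all analyses are ITT with ITT plus one prespecified supportive analysis at 2 h and at 6 h. In it:

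- Patients switched to NIV, intubated or dead before the sample stay in their assigned arm.
- They are ranked worst, or given the worse (higher) of baseline and last pre-switch PaCO2, instead of the value on rescue. Choose one rule in advance. Baseline alone is not enough, because it may be better than the true state of a patient who worsened.
- Noninferiority of HFNT itself is claimed only if this analysis agrees with ITT. Otherwise the conclusion is worded as HFNT first with NIV rescue.

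A per-protocol set may be added, but one that simply excludes rescued patients should not be the only safeguard. Report the number on rescue NIV at each sample. Leave the bedside rescue criteria unchanged.

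**Cost.** Changed analysis wording and one extra analysis. The article lists device settings at 2 and 6 h but not switch time, so confirm that the case report form records the device in use and the switch time. The claim becomes slightly harder to win. The article reports the trial as still recruiting, so the rule could be set before analysis.

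### The 10 mmHg margin is set on the mean scale, but the plan leaves the primary 2 h PaCO2 comparison to either a t test or a Mann–Whitney test and does not fix one estimate to hold against it

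*Protocol article*

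**What the plan says.** All of this stands in the Protocol article, Statistical analysis, unless another section is named.

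- Sample size: "we computed a sample size of 56 patients", "with a standard deviation for the primary outcome equal to 15 mmHg" and "a noninferiority limit of 10 mmHg", at a one-sided 5% level. A further 30% for drop-outs and "an increase in sample size for nonparametric analysis (15"%) lead to 80 patients, 40 per group.
- Distribution: the sentence that opens "After checking the Gaussian distribution" goes on to say whether means or medians will be shown. It does not mention tests.
- Tests: "Continuous data will be compared by the Mann–Whitney" test or Student's t test. No rule for choosing is given, and the primary outcome is not singled out. Another sentence assigns the Kruskal–Wallis test to between-group differences at baseline, 2 h and 6 h. With two groups that is also a rank test.
- Decision: significance is p below 0.05. The section does not say how a result will be set against the 10 mmHg.

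Study endpoints makes noninferiority on PaCO2 at 2 h the primary question. Data collection and outcome assessment records arterial blood gases shortly before randomization, so a baseline PaCO2 exists for every patient. The analyst is to be blinded to allocation.

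**The concern.** A noninferiority margin has meaning only for a named quantity. Here the margin and SD are in mmHg and were used as a difference in means. A Mann–Whitney test gives a rank p-value. Even if it is turned into a shift in mmHg, that shift equals the mean difference only when the two distributions have the same shape.

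The direction of any discrepancy matters. Suppose a minority of HFNT patients do not clear CO2. They raise the HFNT mean, make a normality check more likely to fail, and then count for less in the rank test that the failed check brings in. In a noninferiority trial that would help the new treatment. The protocol itself allows for poor responders: it counts a fall of less than 10 mmHg as treatment failure and permits rescue NIV in the HFNT arm. The question is how much the open choice of test could move the false-noninferiority rate.

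**Working it through.** **1. The plan's own figure.** Inputs: margin Δ = 10, SD σ = 15, one-sided α = 0.05, 1:1 allocation (Study design). Two inputs are read in: power of 80% (the text prints "a β error of 80"%, but only 80% power gives 56) and a true difference of 0.

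n per arm = 2(z₀.₉₅ + z₀.₈₀)²σ²/Δ² = 2 × (1.645 + 0.842)² × 225/100 = 27.8, so 28 per arm and 56 in total. This reproduces the stated figure and confirms that the margin was calibrated to a difference in means.

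**2. Why the two tests can disagree at the margin.** Assume NIV ~ N(60, 12). Let HFNT have mean 70, with 20% of patients 30 mmHg above the rest and SD 12 within each part. The tail adds 0.2 × 30 = 6 to the mean, so the other 80% centre on 64. Subtract the margin: 80% of HFNT centres on 54 and 20% on 84, against 60 for NIV. The mean difference is exactly zero, so a mean-based test is at its null. The rank test looks at P(HFNT − 10 < NIV). With SD √(12² + 12²) = 16.97:

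0.8 × Φ(6/16.97) + 0.2 × Φ(−24/16.97) = 0.8 × 0.638 + 0.2 × 0.079 = 0.526.

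This exceeds 0.5, so the rank test leans towards noninferiority although the mean deficit is the full 10 mmHg.

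**3. Simulated false-noninferiority rate.** The true mean difference is exactly 10 mmHg, 40 per arm, one-sided 5%, 8,000 runs per row (standard error near 5%: √(0.05 × 0.95/8000) = 0.24 percentage points). SD is 15 unless stated. Switch means Mann–Whitney on margin-shifted data if Shapiro–Wilk p < 0.05 in either arm, otherwise the t test.

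| Assumed shapes | Fixed t test | Switch |
|---|---|---|
| Both normal | 5.2% | 5.3% |
| Same lognormal in both | 5.0% | 4.9% |
| Same exponential in both | 5.0% | 5.1% |
| Same t (4 df) in both | 5.1% | 5.2% |
| Same mixture in both | 5.3% | 5.5% |
| HFNT 15% poor responders (+30), NIV normal | 5.4% | 7.2% |
| HFNT mildly right-skewed, NIV normal | 5.0% | 7.8% |
| HFNT strongly right-skewed, NIV normal | 6.3% | 13.1% |
| Both right-skewed, SD 18 HFNT, 12 NIV | 7.0% | 21.6% |
| Both right-skewed, SD 12 HFNT, 18 NIV | 3.6% | 0.7% |
| HFNT left-skewed, NIV normal | 3.8% | 1.4% |

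**4. The 20%, +30 mmHg mixture, by where the tail lies** (6,000 to 8,000 runs; 28 and 40 per arm):

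| Tail | Switch, 28 per arm | Switch, 40 per arm |
|---|---|---|
| HFNT only, component SD 12 | 7.6–7.8% | 8.5–9.2% |
| HFNT only, component SD 10 | 9.0–9.6% | 10.5–11.4% |
| 20% HFNT, 10% NIV | 5.8% | 6.3% |
| Same tail in both arms | 4.6% | 5.9% |
| NIV only | 4.3% | 3.9% |

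For the component SD 10 row, the HFNT SD is √(10² + 0.2 × 0.8 × 30²) = 15.6 and a fixed t test gives 5.5–6.0%. A milder HFNT-only mixture (30%, +25) gives 5.7–7.5% under switching. A more extreme one (15%, +40) gives 12.6–20.5%.

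**5. The 15% allowance.** Drop-out alone: 56/0.70 = 80. Adding the percentages: 56 × 1.45 = 81.2. Compounding: 56 × 1.15 × 1.30 = 83.7, 56 × 1.15/0.70 = 92, or 56/(0.70 × 0.85) = 94.1.

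**The case against.** The strongest reply is that the mechanism simulated above is not written in the article. The distribution check governs presentation, and its link to the test is a natural reading but an inference. The Shapiro–Wilk rule and the margin-shifted rank test are constructions needed to compute anything. This stands, so the rates illustrate one plausible reading and do not describe a stated rule.

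Second, the direction depends on assumed shapes. The Discussion lists discomfort and poor patient–ventilator interaction as drawbacks of NIV, so a tail of poor responders in NIV, or in both arms, is just as arguable. This also stands: in those cases the switch gives about 4 to 6%. A reader might infer that the plan carries a false-noninferiority rate of 10 to 20%. The documents give no distribution, and figures of that size need a strong or extreme asymmetry against HFNT.

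Third, the analyst is blinded. That limits picking the test that suits one arm, but it does not change the error rate of a rule driven by the shape of the data.

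Fourth, an article condenses, and a fuller plan may name the primary test. That may be so. But the article does more than leave a gap: it offers two tests with different targets beside a margin tied to one of them, and its sample-size text foresees a rank analysis.

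Finally, a reader might infer that 80 patients fail to cover the 15% allowance. That depends on convention. Compounding gives about 84 to 94, but simple addition gives 81.2, close to 80. It cannot carry the point.

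**Conclusion.** The point holds in a limited form. The margin and SD are calibrated to a difference in means (56 reproduces exactly), the primary comparison may be made on means or ranks, and neither test as described yields an mmHg estimate to hold against 10 mmHg.

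The size is conditional. With a poor-responder tail in HFNT only, a normality-driven switch gives roughly 7 to 10% false noninferiority, more in extreme cases, against 5 to 6% for a fixed t test. It stays at about 5% when the arms share a shape and falls below 5% when the tail is in NIV. All shapes are assumptions, and no single inflated rate can be attributed to the plan. The case for change rests on the mismatch between margin and method and on how little the remedy costs. It does not need a claim that the trial is biased towards HFNT.

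**What to change.** State one primary analysis that applies whatever the distribution: the mean difference in 2 h PaCO2, HFNT minus NIV, adjusted for baseline PaCO2. Conclude noninferiority if the upper limit of the two-sided 90% confidence interval (one-sided 95%) is below 10 mmHg. Report the Hodges–Lehmann shift with its confidence interval as a sensitivity analysis. Confine the t test or Mann–Whitney wording, and the distribution check, to other continuous outcomes and to presentation.

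With a mean-based primary analysis the 15% nonparametric allowance is no longer needed. The sample-size text can then say that 80 = 56/0.70 reflects drop-out alone. The number of patients does not change.

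The cost is one paragraph and no new data, since blood gases are already taken at inclusion. Trial status shows recruitment still open, so the choice can be dated before analysis. The downside is slightly lower efficiency if outliers are extreme, which the sensitivity analysis would show. A fixed t test is not exact either when shapes or spreads differ (3.6 to 7.0% in the scenarios of step 3), but it stays much closer to 5% than the switch. The baseline-adjusted version was not itself simulated.
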